#### Association between demographic and clinical characteristics and range of movement outcomes in LBP subjects

Pearson correlation coefficients will be used to assess the univariable association between range of movement and various back pain subject characteristics. Multivariable associations will also be assessed using multivariable Pearson correlation coefficients and multivariate linear regression analysis. In determining multivariable models, collinearity between potential variables will first be assessed and variables where high collinearity will be excluded.

The focus on all data analyses will be on those registry participants with complete data. However, we will report rates and reasons for missing data and, where appropriate, consider imputation of missing cases using appropriate statistical methods.

All inferential analysis results will be reported as mean differences and 95% confidence intervals. We will report *P*-values to three decimal places with P-values less than 0.001 reported as *p* < 0.001. All statistical tests will be performed using two-sided tests at the 0.05 level of significance. No formal adjustment of the level of significance for testing will occur, but P-values will be interpreted accordingly, considering the multiple testing outcomes. An analysis will be undertaken at the end of the phase I, upon completion of enrolment of the age and sex-matched cohorts, prior to proceeding with enrolment of phase II of the registry.

All analyses will be undertaken using STATA version 14 [17].

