**Methods:**

This ongoing, non-randomized, prospective post-market registry will consist of two groups: patients with LBP, and age and sex-matched controls without LBP. We will seek to recruit 132 subjects in each group. Data collection will take place in two phases: (1) baseline assessment of LBP patients and matched controls; (2) assessment of LBP patients at 6 and 12-months follow up. The primary outcome measure will be differences in movement patterns between those with LBP and those without LBP. Secondary outcomes will include differences in patient reported outcomes including pain, disability and quality of life.

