## Methods/design

This is an ongoing, non-randomized, prospective post-market registry consisting of two groups: patients with LBP, and age and sex-matched controls without LBP. We will recruit a total of 132 subjects in each group. B-PAM has a flexible design to allow new dorsaVi products to be added to the registry following their market release. Data collection will take place in two phases: (1) baseline assessment of LBP patients and matched controls; (2) assessment of LBP patients at 6 and 12-months follow up.

Reporting and data analysis of the B-PAM registry will be undertaken in accord with The Strengthening the Reporting of Observational Studies in Epidemiology (STROBE) guidelines for reporting observational studies [14].

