### Subject selection

Subjects with LBP will be included if they fulfil the following criteria:Subject or legally authorized representative provides written authorization and/or consent per institution and geographical requirementsSubject with a predominant complaint of LBP of any duration, with a minimum daily pain average visual analogue score (VAS) ≥ 30/100Subject is intended to be assessed with the eligible product

Exclusions to enrollment are:Unable to be available for study follow-upsExclusion criteria required by local lawMovement assessment is contraindicated for any reason.Currently enrolled in or plans to enroll in any concurrent drug and/or device study that may confound resultsBody mass index ≥35 kg/m^2^

Controls will be recruited using study advertisement flyers posted on campus at the George Washington University, local gymnasiums, recreational centers, via word of mouth, and email list servers associated with educational programs within The George Washington University School of Medicine and Health Sciences. Subjects will be screened by phone for the presence or history of LBP (no current LBP and no history of LBP lasting longer than 3 months in the past 12 months) as well as other exclusion criteria listed above. Controls will be age and sex-matched with LBP patients on a one-to-one basis.

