### Sample size

Detection of a ‘moderate’ effect size (i.e. Cohen’s effect size of ≥0.40 in range of movement and other outcomes) between LBP and controls requires 132 individuals per group at 90% power and alpha of 5% (estimated using STATA’s sampsi command) [15].

Based on this sample size and using data in individuals with no back pain reported by Laird (Monash University, Research Project Report No: cf11/0748–2,011,000,372), Table 1 shows the predicted minimum mean difference that could be detected between back pain and control groups. The magnitude of these predicted between-group differences in range of movement appear to be fairly consistent with those reported in the meta-analysis conducted by Laird et al., evaluating previously published studies comparing LBP and control populations [3].

**Table 1 Tab1:** Range of motion and predicted minimum mean differences between back pain and control groups

ROM outcome	Non-back pain group Observed Mean (SD)	Predicted minimum mean difference between control and back pain group
Lordosis		
30–39 years	-30 (6.9)	± 2.76
40–49 years	−32 (10.1)	± 4.04
50–65 years	− 36 (12.2)	± 4.88
Standing flexion		
30–39 years	46 (11)	± 4.4
40–49 years	48 (6)	± 2.4
50–65 years	46 (9)	± 3.6
Standing extension		
30–39 years	−26 (10)	± 4.0
40–49 years	−18 (11)	± 4.4
50–65 years	−17 (14)	± 5.6

We have also estimated the impact sample size of 132 back pain individuals in terms of achieving our second research objective of assessing the subject demographic and clinical characteristics associated with range of movement. Based on the rule of thumb of 10 observations needed per covariate (or predictor) [16], 32 individuals with back pain would allow for a multivariable regression including up to 13 covariates. 132 subjects would also allow detection of an increase in the f2 of multivariable model with 9 covariates from 50 to 55% with the inclusion in the model of one additional covariate at 90% power and 5% alpha (using STATA’s powerreg command) [17].

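### Making complete-data participants the focus of every analysis exposes the 6 and 12-month LBP changes to attrition bias, and the target of 132 per group leaves no margin for missing baseline outcomes

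*Protocol article*

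**What the plan says.** **Analysis set.** The closing paragraphs of the Statistical analysis section say: "The focus on all data analyses will be on those registry participants with complete data". The sentence stands under the subsection on associations in LBP subjects, but its wording covers all analyses. The next sentence promises a report of how much is missing and why, and says the authors will "where appropriate, consider imputation of missing cases using appropriate statistical methods".

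**Longitudinal analysis.** The subsection on comparing range of movement and secondary outcomes plans to examine changes from baseline to follow-up within groups. Under Methods/design and Measurements, only LBP patients return at 6 and 12 months. The Ethical approval section foresees exits through withdrawal, poor compliance or unavailability, and states no rate.

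**Sample size.** Detecting "Cohen’s effect size of ≥0.40 in range of movement and other outcomes" is said to be a target that "requires 132 individuals per group at 90% power and alpha of 5" per cent. Methods/design sets recruitment at the same number: "We will recruit a total of 132 subjects in each group". The document gives no expected rate of missing data.

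**The concern.** Two consequences follow from the same sentence and need to be kept apart.

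The first and more important one is bias. A complete-case estimate of change at 12 months describes the patients who came back. If recovery, persistent pain or poor function influences attendance, their mean change is not the mean change of the cohort enrolled. A patient who attended at baseline and 6 months but missed 12 months adds nothing to a complete-case 12-month estimate, although those two assessments carry information about the missing one.

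The second is margin. The calculated requirement and the recruitment target are the same number, and the main analyses rest on complete records. The stated 90% therefore holds only if every recruited person supplies a usable baseline outcome.

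**Working it through.** **Inputs.** Effect d = 0.40, power 90%, alpha 5% and 132 per group come from Sample size. Two-sided testing comes from Statistical analysis ("All statistical tests will be performed using two-sided tests at the 0.05 level of significance"). The protocol gives no rate of missingness, so the rates below are assumptions.

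**1. Reproduce the plan's figure.**
n per group = 2(z₀.₉₇₅ + z₀.₉₀)² / d² = 2(1.960 + 1.2816)² / 0.16 = 131.3, rounded up to 132. The protocol's number is confirmed.
Power at 132 by the normal approximation is Φ(0.40·√(132/2) − 1.960) = Φ(3.250 − 1.960) = 90.1%. With the t distribution it is 89.9%. There is no slack.

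**2. Baseline contrast with some outcomes missing** (two-sample t-test, n = 132 × (1 − m) per group):

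| Assumed missing m | n analysed per group | Power for d = 0.40 | Recruit per group to keep 132, 132/(1 − m) |
|---|---|---|---|
| 0% | 132 | 89.9% | 132 |
| 5% | 125.4 | 88.4% | 139 |
| 10% | 118.8 | 86.7% | 147 |

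Rounding n down to whole subjects, or using the normal approximation, moves these power figures by about 0.3 points or less.

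**3. Does follow-up dropout enter step 2?** The protocol measures LBP patients and controls at enrolment and follows only LBP patients. I take the powered LBP-control contrast to be the enrolment one. On that reading, losses at 6 and 12 months leave its n unchanged.

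**4. Possible offset from adjustment.** If covariates explain a share R² of the outcome variance, the residual SD becomes √(1 − R²). With an assumed R² = 0.10, power by the normal approximation is 92.9% with no loss and 89.9% with 118 per group. The Sample size section does not claim this gain.

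**5. Within-LBP change: power or bias?** For a change of 0.40 baseline SD, with correlation ρ between visits, the standardised change is 0.40/√(2(1 − ρ)).
- Assumed ρ = 0.5: standardised change 0.40. This needs 68 completers for 90% power, and 30% dropout leaves 92 patients and 96.7%.
- Assumed ρ = 0.3: standardised change 0.338. This needs 94 completers, and 30% dropout gives 89.4%.

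Power for change is therefore not the main difficulty. Bias is. If a fraction p drops out, the completers' mean differs from the full-cohort mean by p × (mean change in completers − mean change in dropouts). As an illustration only, with p = 0.20 and a gap of 0.40 SD between the two, the bias is 0.20 × 0.40 = 0.08 SD. A larger sample does not reduce it.

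**The case against.** The strongest reply is that the power statement concerns a single in-person assessment at enrolment, where few movement outcomes should be missing. At an assumed 5 to 10% the unadjusted loss is only about 1.5 to 3 points, and covariate adjustment may recover it. The plan excludes at entry people who cannot attend follow-up, undertakes to report rates and reasons for missing data, and leaves imputation open. Its method and trigger may properly sit in a statistical analysis plan that is not shown. The within-group changes are secondary, and no power is claimed for them.

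Much of this stands. The power loss is modest and conditional, and the absence of an imputation method from an article is not a fault. But the document does fix a main approach, and for longitudinal change it is not the best one available. The entry exclusion and the reporting of reasons reduce or describe attrition; they do not correct for it.

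Three stronger readings are tempting but unsupported:
- *That 90% power is not delivered.* This depends on missing baseline outcomes, whose rate is unknown.
- *That one missing item or one missed visit removes a patient altogether.* Completeness is not defined that way. Several questionnaires in Table 3 are not collected from controls, so completeness on every item cannot be the rule for the group contrast. A patient seen at baseline and 12 months could still count in the 12-month change.
- *That losing a case or its control ruins the matching.* Enrolment is matched ("Controls will be age and sex-matched with LBP patients on a one-to-one basis"), but the planned analysis is regression adjusted for the matching variables, not a paired analysis. An unpaired subject still contributes.

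**Conclusion.** The point holds in two limited parts.

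1. Complete-case analysis as the main approach puts the 6 and 12-month LBP changes at risk of attrition bias and makes poor use of partial records. The size cannot be derived from the document, because it gives neither a dropout rate nor the difference between completers and dropouts. The concern rests on the plausible assumption that attendance relates to pain or movement.

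2. The 132 per group is correctly calculated but has no allowance for missing baseline outcomes. Nominal unadjusted power falls from 89.9% to about 88.4% at an assumed 5% missing and 86.7% at an assumed 10%. Follow-up dropout plays no part in this, given the enrolment contrast.

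The first part justifies a change of method. The second calls for an honest statement of what the 90% assumes.

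**What to change.** - **LBP change:** make the main analysis a linear mixed model on the 0, 6 and 12-month assessments that includes every LBP patient with at least one assessment.
- **Baseline contrast:** include everyone with the outcome in question and multiply impute missing covariates, so that nobody is lost for a covariate alone.
- **Complete-case analysis:** keep it as a sensitivity analysis.
- **Sample size text:** state that 90% power assumes 132 analysed outcomes per group, and give the power at an assumed 5 to 10% of missing baseline outcomes (88.4% and 86.7%). Imputing covariates does not restore missing outcomes, so these figures refer to outcomes only.

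The cost is revised wording and a little more analysis work with standard Stata commands. The stated power becomes slightly less favourable. The mixed model and the imputation rely on missing at random. That is a weaker assumption than complete-case analysis of change needs, but it does not remove bias if dropout depends on unobserved pain or movement.

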### Data and quality management

Data will be collected using an electronic data management system and hard copy forms. Data reporting will be completed and submitted by the investigator or authorized staff. All data will be stored in a secure, password-protected database with a hard-copy backup in a locked file cabinet. Access will be controlled as delegated by dorsaVi to either a contract research organization (CRO) or to the principal investigator’s clinical site. This will allow for independent management of the data, which will be blinded to the investigators. The database will be backed up regularly.

The role of the CRO or Principal Investigator’s site would include data checking, data cleaning and data scoring. Ultimately, a scored/cleaned data set would then come to the study statistician to run the actual data analyses, further this data set would be provided to dorsaVi. dorsaVi may delegate an entity (CRO) to review site reported data to monitor quality. Data discrepancies will be highlighted as required and forwarded to the site for resolution. Site personnel are responsible for the timely submission or data and the resolution of discrepancies per their standard of care practices.

## Discussion

The Back Pain and Movement (B-PAM) registry provides the infrastructure to utilize the dorsaVi system to objectively measure movement and muscle activity in order to better understand movement patterns in LBP and non-LBP control populations. Furthermore, movement signatures among cohorts with similar diagnoses may be identified.

### Back pain registries

There are several ongoing registries that collect similar data. The Back-Pain Outcomes Using Longitudinal Data (BOLD) project specifically focused on those older than 65 with a new episode of LBP. This registry collects data including diagnostic tests, current treatments, pain, health-related quality of life and functional disability. Spine IQ is a registry specifically focused on performance measures. Designed to describe the natural history of disease, determine the clinical effectiveness of health care services and to measure/monitor safety and quality, it is focused on assisting U.S. clinicians with the transition to value-based care as mandated by U.S. legislation. Neither registry seems to focus on a deeper understanding of movement and its contributions to LBP. Furthermore, understanding patterns of movement as they relate to specific diagnoses are not emphasized.

### Strengths and limitations

Registries have the advantage that they enable easier patient enrolment than intervention trials such that large sample sizes are feasible. This increases the external validity, generalizability, and real-world applicability of data collected in registries. The non-observational nature of registries means that they are subject to confounding, selection bias, and poor data quality control. We have sought to minimize these limitations in B-PAM by use of age and sex matching of LBP controls, and through rigorous application of measures to ensure data quality.

### Future plans

We plan to extend the recruitment to additional US sites at a later date based on the following criteria:Clinicians familiar with and representative of the dorsaVi product;A patient population with more than 50 new LBP patients visiting monthly;Sites with adequate resources, facilities, equipment and support staff;Site is able to comply with registry requirements as well as local laws and regulations and dorsaVi requirements.

## Abbreviations

B-PAM: Back Pain and Movement Registry
DASS: Depression, Anxiety and Stress Scale
EQ-5D: EuroQol – 5D
FABQ: Fear-Avoidance Beliefs Questionnaire
ICD-10: International Classifications of Disease – 10
LBP: Low-Back Pain
ODI: Oswestry Disability Index
QVAS: Quadruple Visual Analogue Scale
STROBE: Strengthening the Reporting of Observational Studies in Epidemiology
USA: United States of America
VAS: Visual Analogue Scale
